## Discussion

The aim of our trial is to investigate the feasibility and observe the efficacy of the ICBT programme FearFighter™ for people with anxiety disorders in Denmark. We expect to widen the scope of this relatively new area of research on Internet-based therapy as the conducted Danish trial on FearFighter™ demonstration project failed to recruit the intended number of participants and suffered from a participant dropout rate of 50 % in the intervention group [19].

Our trial is being conducted in cooperation with the CTU, a centre for clinical intervention research. The design of this trial is in accordance with the guidelines provided by the SPIRIT Statement [20] and the standard operating procedures, developed and maintained by the CTU in order to secure the validity and reliability of the trial results [42]. We have tried our utmost to reduce risks of bias [23, 24, 43–47] by employing centralised randomisation, blinding of outcome assessors, blinding during data management, blinded statistical analyses, and blinded drawing of conclusions to fulfil national and international standards of Good Clinical Practice [48].

Our criteria for inclusion and exclusion are few because we believe that the results of our trial will have a potentially wide generalisability. It should be also noted that the participants will be recruited among visitors to the Student Counselling Service’s homepage. Therefore, we may expect that the participants, students from Danish universities suffering from an anxiety disorder, to be rather homogenous concerning duration and severity of symptoms, age, cultural and economic background, and a low prevalence of comorbidity, which otherwise may limit the generalisability of the results to more clinically heterogeneous samples.

We will consider our feasibility trial sufficiently successful if more than 50 % of the eligible participants are randomised and if more than 60 % of the 32 randomised participants complete FearFighter™. A satisfactory feasibility outcome value will warrant a future large-scale trial to investigate further the observed efficacy and the cost-benefit of FearFighter™.

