**Methods and design:**

We will conduct an investigator-initiated, feasibility randomised controlled trial. Sixty-four participants are expected to be recruited via an advertisement posted on the homepage of the Student Counselling Service in Denmark. The inclusion criterion for participation in the trial will be the presence of anxiety disorder as assessed with the Mini International Neuropsychiatric Interview. The exclusion criteria will be suicidal risk, an ongoing episode of bipolar disorder or psychosis, concurrent psychological treatment for the anxiety disorder, considered unable to attend the intervention as planned (due to vacation, work/study placement, sickness, or similar occurrences), or lack of informed consent. The intervention group will be offered nine sessions with the ICBT programme FearFighter™ and a weekly telephone contact to support compliance. The control group will receive no intervention. We define the feasibility outcomes as follows: the fraction of randomised participants out of the eligible people (the lower 95 % confidence interval (CI) ≥ 50 %); and the fraction of compliant participants (those receiving at least six out of nine sessions) in the intervention group (the lower 95 % CI ≥ 60 %). The exploratory clinical outcomes are the number of participants no longer meeting the diagnostic criteria for an anxiety disorder at the end of the trial and level of distress (Beck Anxiety Inventory, Symptom Checklist-90-R, WHO Well-Being Index, Sheehan Disability Scale); the number of severe adverse events; and the occurrence of any psychological treatment outside the trial.

To prevent bias in design, and in the gathering and analysis of data throughout the trial, we will follow the SPIRIT 2013 statement which defines standard protocol items for clinical trials.

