### Sample size

The primary feasibility outcome is the number of randomised participants divided by the number of all eligible people for the trial. Eligible people are those who fulfil the inclusion criteria of our trial. If the number of randomised participants is 64 out of 100 eligible people then the proportion will be 64 % with 95 % confidence interval (CI) between 50 and 78 %. A proportion of 50 % or more randomised participants will be acceptable for a future trial. In contrast, if the likely sample proportion is less than 50 %, we will have difficulties with recruiting participants for a large trial as well as with generalisability of results.

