### Statistical analyses

The primary feasibility outcome is defined as the number of participants randomised out of the people considered eligible for being randomised in the trial. Based on observations regarding pretreatment attrition in CBT and IBT for anxiety disorders studies [9, 36–38], we will consider the feasibility outcome satisfactory if it is over 50 %. Our hypothesis is that we are sampling from a population of eligible people of whom at least half will be randomised. If we let *N* be the observed number of eligible people needed to randomise a sample of 64 participants, then in a random sample of size *n* sampled from a population sized *N*, *n/N* follows a binomial distribution with a lower 95 % CI of over 50 % [39, 40]. The sample size estimated from the primary feasibility outcome implicitly defines the sample sizes to be used in the assessment of the exploratory clinical outcomes (Table 1).

The secondary feasibility outcome for the participants in the experimental group is defined as the number of participants completing at least six out of nine FearFighter™ sessions. This feasibility outcome is considered satisfactory when the lower 95 % CI is over 60 % based on observations for completer fractions in IBT for anxiety disorders [9, 41]. In a random sample of size *n* of completers sampled from a population sized *N* of participants in the experimental group, *n*/*N* follows a binomial distribution with a lower 95 % CI over 60 %.

The exploratory clinical outcomes will be analysed using the general linear model (GLM) logistic regression, or the proportional odds model for ordinal outcomes as appropriate, adjusting for the stratification variables and baseline scores of the outcomes according to Table 2. We will calculate two-sided tests and use the resulting *p* values as a data-reducing device because test results with *p* values < 0.05 will be used to select hypothesis-generating outcomes.

**Table 2 Tab2:** Feasibility outcomes and exploratory clinical outcomes in the Fearfighter™ feasibility trial

	Rating scales	Type of outcome	Test
Feasibility outcome			
Number of randomised participants/eligible persons	Not relevant	Proportion	Calculate the probability that 64/*N* can have been obtained in a random sample of *N* participants obtained from a population of persons where half the eligible persons can be randomised. (*N* is the observed number of eligible persons necessary to examine to randomise 64 participants)

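### The feasibility success rule is worded in some places as a lower 95 % confidence limit and in others as an observed proportion, and plausible results pass one form and fail the other.

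*Protocol article*

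**What the plan says.** **Recruitment (randomised out of eligible).**
- Abstract, Methods and design: "the fraction of randomised participants out of the eligible people (the lower 95 % confidence interval (CI) ≥ 50" %. This is a lower-limit rule.
- Statistical analyses, first paragraph: "we will consider the feasibility outcome satisfactory if it is over 50" %. This is worded on the proportion itself. Later in the same paragraph the proportion "follows a binomial distribution with a lower 95 % CI of over 50" %, which is a lower-limit condition.
- Sample size: "A proportion of 50 % or more randomised participants will be acceptable for a future trial". This follows a worked example of 64 out of 100 with a stated lower limit of 50 %, so its meaning is less clear.
- Discussion: "sufficiently successful if more than 50 % of the eligible participants are randomised and if more than 60 % of the 32 randomised participants" complete the programme. This is worded on observed proportions for both outcomes.

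**Compliance (at least six of nine sessions, experimental group).**
- Abstract: "in the intervention group (the lower 95 % CI ≥ 60" %.
- Statistical analyses: "This feasibility outcome is considered satisfactory when the lower 95 % CI is over 60" %.
- Table 2 describes a test meant to rule out a population whose compliance is below 60 %. It states no confidence limit.
- Only the Discussion uses the observed proportion.

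The Discussion adds that a satisfactory feasibility result would justify a large trial, so this is the go/no-go rule.

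**The concern.** An observed proportion above a threshold and a lower confidence limit above it are different hurdles, and at these sample sizes they lie far apart. The observed-proportion form is always the easier one. The conflict therefore runs one way: a result can pass the Discussion's rule and fail the lower-limit rule, never the reverse.

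These are the primary and secondary outcomes of a feasibility trial, and the go decision rests on them. If both forms remain, the team can report success or failure from the same counts and point to the article either way. The blinded drafting of conclusions does not guard against this for compliance, because the Blinding section says compliance conclusions cannot be blinded.

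**Working it through.** **Inputs from the protocol article.** 64 randomised (abstract; Statistical analyses); 32 in the experimental group (Support person and support manual; Discussion); thresholds of 50 % and 60 %. The article names no interval method, so Wald, Wilson and exact (Clopper-Pearson) limits are all used, two-sided 95 %.

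**The plan's own figure.** Sample size gives 50 to 78 % for 64/100. The Wald interval is 0.64 ± 1.96 × √(0.64 × 0.36/100) = 0.64 ± 0.094, or 54.6 to 73.4 %. The exact interval is 53.8 to 73.4 % and the Wilson interval 54.2 to 72.7 %. The stated interval is not reproduced. That is a separate error, and nothing below depends on it.

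**Recruitment, 64 out of N.**
- Observed-proportion rule: 64/N > 0.50 requires N < 128, so it passes up to N = 127 (64/127 = 50.4 %). Read literally, the Sample size wording would also admit N = 128, which is exactly 50 %.
- Lower-limit rule:

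| N | 64/N | Wald | Wilson | Exact |
|---|---|---|---|---|
| 106 | 60.4 % | 0.511 | 0.509 | 0.504 |
| 107 | 59.8 % | 0.505 | 0.503 | 0.499 |
| 108 | 59.3 % | 0.4999 | 0.498 | 0.494 |
| 127 | 50.4 % | 0.417 | 0.418 | 0.414 |

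It passes up to N = 106 (exact) or 107 (Wald, Wilson). The verdicts differ from N = 107 or 108 up to 127.

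**Compliance, k out of 32.**
- Observed-proportion rule: 0.60 × 32 = 19.2, so it passes from k = 20 (62.5 %).
- Lower-limit rule:

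| k | k/32 | Wald | Wilson | Exact |
|---|---|---|---|---|
| 20 | 62.5 % | 0.457 | 0.453 | 0.437 |
| 22 | 68.8 % | 0.527 | 0.514 | 0.500 |
| 24 | 75.0 % | 0.59997 | 0.579 | 0.566 |
| 25 | 78.1 % | 0.638 | 0.612 | 0.6003 |

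All three methods first pass at k = 25. The verdicts differ for k = 20 to 24.

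**Chance of passing compliance,** with X binomial (32, p):

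| True p | P(X ≥ 20), observed proportion | P(X ≥ 25), lower limit |
|---|---|---|
| 50 % | 0.11 | 0.001 |
| 60 % | 0.46 | 0.025 |
| 70 % | 0.87 | 0.21 |
| 75 % | 0.96 | 0.43 |
| 80 % | 0.99 | 0.70 |
| 85 % | > 0.99 | 0.90 |

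**Sensitivity to a one-sided reading.** With a one-sided 95 % limit, the recruitment cut-off becomes N = 109 (exact) or 110 (Wald, Wilson), and the compliance cut-off 25 (exact) or 24 (Wald, Wilson). The conflict remains.

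**The case against.** The best defence is that the lower limit is the real rule and the other wording is shorthand. Much of this is fair.

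- In Statistical analyses, the sentence on exceeding 50 % can be read as naming the target, which the lower-limit sentence in the same paragraph then makes operational.
- The Sample size sentence follows an example whose stated lower limit is exactly 50 %, so it may have been meant as the lower-limit rule.
- For compliance, the abstract, Statistical analyses and Table 2 all call for inference against 60 %. A Discussion normally summarises the methods.

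What survives is that the Discussion sentence is framed as the criterion for success, with its own denominator of 32, and is followed directly by its consequence for a future trial. No sentence subordinates it to the methods. This is a conflict inside the published text, not a detail left to a separate analysis plan.

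Three stronger readings are tempting and are not supported:
- That the two forms are spread alike across the article for both outcomes. The 60 % observed-proportion rule appears only in the Discussion.
- That Table 2 sets a lower confidence limit. It describes a test, and for recruitment only a probability to be calculated, with no cut-off.
- That the observed-proportion rule gives no protection against poor compliance. It passes 46 % of the time at a true 60 %, but 11 % at 50 %. Protection is weak near the boundary, not absent.

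**Conclusion.** The concern holds as a contradiction in the go/no-go rule. It is wider for recruitment, where both forms stand in Statistical analyses, than for compliance, where the Discussion alone departs. Opposite verdicts arise for 107 or 108 to 127 eligible people (about 50 to 60 % randomised) and for 20 to 24 completers of 32 (62.5 to 75 %). These are realistic results for a trial of this kind.

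The counts assume exactly 64 randomised and 32 in the experimental group. Stratified randomisation with varying block sizes does not guarantee the second: the exact cut-off would be 24 of 30, 25 of 31 or 26 of 33. The choice of interval moves the recruitment cut-off by one person and leaves the compliance cut-off at 25. The probabilities assume independent participants with a common chance of completing.

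A reader might infer that the double wording was meant to leave room for choosing the verdict later. The article does not suggest that; it only fails to exclude it.

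**What to change.** 1. Make the lower 95 % confidence limit the single success rule for both outcomes and name one interval method. The exact two-sided interval is a reasonable choice but not the only one.
2. Align the Sample size sentence, the recruitment sentence in Statistical analyses and the Discussion sentence with that rule. For compliance, only the Discussion needs changing. Use either at least or more than throughout; the abstract and Statistical analyses currently differ.
3. Give the implied counts under the exact interval as illustrations: at most 106 eligible people for 64 randomised, and at least 25 completers of 32. Say that they will be recomputed if the actual numbers differ.
4. State the chance of passing the compliance rule: 21 %, 43 %, 70 % and 90 % at true compliance of 70, 75, 80 and 85 %.

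The edits are to wording, but they have a price. The visible bar rises to about 60 % observed for recruitment and 78 % for compliance. Item 4 also shows openly that, with 32 participants, a programme with 75 % true compliance would more often fail than pass. The sponsor should accept that knowingly.

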### Trial status

This trial will begin recruiting participants in August 2015. The last participant of the 64 participants will be included in May 2016. We estimate to have collected post-treatment data by summer 2016 and follow-up data by winter 2016.

## Abbreviations

ANX: Anxiety dimension
BAI: Beck Anxiety Inventory
CBT: Cognitive behavioural therapy
CI: Confidence interval
DSM-IV: *Diagnostic and Statistical Manual of Mental Disorders – 4th edition*
ES: Effect size
GSI: Global Severity Index
IAPT: Improving Access to Psychological Therapies
IBT: Internet-based self-help therapy
ICBT: Internet-based cognitive behavioural therapy
IS: Interpersonal sensitivity dimension
M: Mean
MINI: Mini International Neuropsychiatric Interview
*N*: Number in population
*n*: Number in sample
NICE: National Institute of Health and Care Excellence
PHOB: phobic anxiety dimension
RCT: Randomised controlled trial
SAPAS: Standardised Assessment of Personality Abbreviated Scale
SCL-90-R: Symptom Checklist-90 revised
SD: Standard deviation
SDS: Sheehan Disability Scale
SMD: Standardised mean difference
SPIRIT: Standard Protocol Items: Recommendations for Interventional Trials
WHO: World Health Organisation
